#### Secondary outcomes

The variation from baseline to 6 months of the Quality of Upper Extremity Skill Test (QUEST), the Pediatric Quality of Life Inventory 3.0 Cerebral Palsy module (PedsQLTM 3.0 CP Module, Parents Report) and the SEP parameters will be analyzed using the cLDA model. For the neuro-orthopedic examination, we will use a chi-square test or Fisher exact test if appropriate. Details the type of trouble will be described in each group without formal statistical comparison.

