### Sample size estimates

Based on the literature [26,27], the mean value of AHA was estimated at 1.8 logit (standard deviation = 2) in the placebo splint group. In the Gordon study [27], an improvement of 48% was obtained with a hand-arm bimanual intensive therapy administrated during 1 month. Based on this study and considering the duration of our therapy (6 months), we expected an improvement of 60% in favor of the Lycra® sleeve (mean AHA = 0.72 logit). Considering a two-sided Student test without adjustment, 53 patients per arm were needed (power 80%, alpha = 5%). The analysis will be adjusted for baseline AHA value, allowing to improve the design efficiency. Assuming a 0.4 correlation between the 2 measures (baseline and post-treatment) corresponding to a relative efficiency of 1.16, 45 patients were required. One hundred patients (50 in each arm) were planned to consider a 10% rate of non-analyzable data.

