##### Body structures and functions measure: neuro-orthopedic examination

Neuro-orthopedic examination is detailed and scored in a standardized way. The examination focuses on mobilities of the impaired arm: flexion and abduction of the shoulder, flexion and extension of the elbow, pronation and supination of the forearm, flexion and extension of the wrist, flexion and extension of the fingers, and abduction of the thumb. Examiner assesses the passive range of motion at high and low speed and gives a score of Modified Ashworth Scale (MAS) for each mobility cited. Active range of motion is recorded for the same mobilities.

The results obtained after this examination are scored so that changes can be analyzed. At the first examination, each mobility is scored on a binary scale (0 = normal range of motion, 2 = presence of anomaly). The results of the second examination, 6 months later, are scored in comparison with the first examination, on a 0 to 3 scale (0 = normal range of motion, 1 = lower anomaly, 2 = stable anomaly, 3 higher anomaly).

On the sensory level, examination details the type of trouble (epicritic, thermoalgesic, and/or proprioceptive defect) during a comparative examination. Both sides impairments are recorded. Examiner reports the absence or presence of a deficit.

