### Statistical analysis

The variation of the Assisting Hand Assessment (AHA) from baseline to 6 months is the primary outcome. Secondary outcomes are the Quality of Upper Extremity Skill Test (QUEST), the Pediatric Quality of Life Inventory 3.0 Cerebral Palsy module (PedsQL™ 3.0 CP Module, Parents Report), SEP parameters (N13-N20 interval, P14-N20 interval, ratios of delay conduction, amplitudes of N20-P27 and amplitude ratio), neuro-orthopedic examination (results of the second examination, 6 months later, scored in comparison with the first examination on a 0 to 3 scale: 0 = normal range of motion, 1 = lower anomaly, 2 = stable anomaly, 3 higher anomaly).

Statistical analyses will be independently performed by the Biostatistics Department of Lille University. Data will be analyzed using the SAS software (SAS Institute Inc, Cary, NC, USA), and all statistical tests will be performed with a 2-tailed alpha risk of 0.05. Baseline characteristics will be described for each group, categorical variables will be expressed as frequencies and percentages, and quantitative variables will be expressed as means and standard deviation in case of normal distribution or medians (interquartile range) otherwise normality of distributions will be assessed graphically and by using the Shapiro-Wilk test. No formal statistical comparisons of baseline characteristics will be done; clinical importance of any imbalance will be noted. For the primary analysis, both analyses (ITT and per-protocol) will be considered to support the conclusion of non-inferiority [45]. ITT population includes all randomized participants based on their original group of randomization. Per-protocol population includes all randomized patients excluding those with major protocol violations: patients who do not complete the rehabilitation procedure allocated after randomization, discontinuation for lack of compliance or personal reasons, adverse reaction. For the secondary objectives, we will use only the ITT population.

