Missing data (whatever the reason) will be handling using the multiple imputation procedure [49,50]. Imputation procedure will be performed using main baseline characteristics and treatment group under missing at the random assumption by using regression switching approach (chained equation with *m* = 20 imputations) with a predictive mean matching method for continuous variables, logistic regression models (binary, ordinal or polynomial) for categorical variables. Imputation procedure will be performed using the baseline characteristics and allocated group. Treatment effect estimates obtained in multiple imputed data sets will be combined using the Rubin’s rules [51]. Complete case analysis will be performed as a sensitivity analysis [52].

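### The neuro-orthopedic endpoint is assigned to all randomized children, but its unadjusted chi-square or Fisher test uses only children scored at 6 months, ignores baseline status as a covariate, and gives no estimate to pool after imputation

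*Protocol article*

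**What the plan says.** Four statements in the Protocol article bear on this endpoint.

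- Population (Statistical analysis): "For the secondary objectives, we will use only the ITT population". The same section defines that set: "ITT population includes all randomized participants based on their original group of randomization".
- Outcome (Body structures and functions measure: neuro-orthopedic examination): each mobility is coded 0 or 2 at the first examination. Then: "The results of the second examination, 6 months later, are scored in comparison with the first examination, on a 0 to 3 scale". Code 0 is normal; codes 1, 2 and 3 are a lower, stable or higher anomaly.
- Test (Statistical analysis, Secondary outcomes): "For the neuro-orthopedic examination, we will use a chi-square test or Fisher exact test if appropriate". QUEST, PedsQL and the SEP parameters are instead analysed with the cLDA model.
- Missing data (Statistical analysis, under the Primary outcome heading): "Missing data (whatever the reason) will be handling using the multiple imputation procedure". The models listed include "logistic regression models (binary, ordinal or polynomial) for categorical variables", treatment effect estimates are combined by Rubin's rules, and "Complete case analysis will be performed as a sensitivity analysis".

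Two further places matter. Patient's eligibility says that the data of discontinued children stay in the intention-to-treat analysis. Sample size estimates says: "One hundred patients (50 in each arm) were planned to consider a 10% rate of non-analyzable data".

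**The concern.** The stated population, outcome, test and pooling rule do not fit together. A chi-square or Fisher test needs a code for every child counted, and the code exists only if the V4 examination was done. The named test therefore delivers the declared ITT set only if no V4 examination is missing. The other formally tested secondary outcomes are not in this position, because cLDA models baseline and follow-up jointly and keeps a child with a baseline value only.

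The imputation paragraph does not clearly close the gap. Its reach beyond the primary outcome is not stated. If it does reach this score, its pooling step needs an estimate with a variance, and a chi-square or Fisher test supplies only a p-value.

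At stake is a spurious arm difference. A mobility that is normal at V2 would be expected mostly to stay normal, so the V4 code depends on V2 status. If one arm loses more of its more affected children, an unadjusted comparison of examined children partly compares different baseline mixes. V2 status, which could correct for this and sharpen the comparison, is recorded but not used as a covariate.

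**Working it through.** **The plan's own figure.** The neuro-orthopedic endpoint has no sample size, power or expected rate, so there is nothing of its own to reproduce. The only figure on loss is the 10% allowance in Sample size estimates, and it reproduces: 45 / (1 − 0.10) = 50 per arm, 100 in total. It is an allowance for non-analyzable data in a calculation for the AHA. No dropout rate is stated. If the whole allowance were missing V4 scores, 45 of 50 children per arm would enter the test.

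**Bias.** Assumptions, none from the documents: one mobility, score reduced to code 0 against the rest, no treatment effect, 60% abnormal at V2, code 0 at V4 in 95% of those normal and 15% of those abnormal at V2, and all losses among children abnormal at V2. With a fraction L of an arm lost, the expected proportion with code 0 among examined children is

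p(L) = [0.40 × 0.95 + (0.60 − L) × 0.15] / (1 − L).

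| Loss by arm | p in each arm | Spurious difference |
|---|---|---|
| 10% / 10% | 0.506 / 0.506 | 0 |
| 14% / 6% | 0.449/0.86 = 0.522; 0.461/0.94 = 0.490 | 3.2 points |
| 16% / 4% | 0.446/0.84 = 0.531; 0.464/0.96 = 0.483 | 4.8 points |

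Simulations of this setting agree (2.9 to 3.2 points and 4.6 to 4.9 points). At 16%/4% the unadjusted test rejected a true null in 7.4% to 8.1% of simulated trials, against 5.6% to 6.0% with no loss. At 14%/6% it rejected in about 6.4% to 6.5%, hardly different from no loss.

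**Effect of using V2 status.** Standardizing the arm difference to the V2 distribution of all randomized children brought the simulated bias at 16%/4% to 0.0 points. The standard error fell from about 0.107 to 0.067.

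The gain does not depend on loss. With all 50 children per arm scored, p = 0.40 × 0.95 + 0.60 × 0.15 = 0.47, and:

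- unadjusted SE = √(2 × 0.47 × 0.53 / 50) = 0.100;
- within-V2 variance = 0.40 × 0.95 × 0.05 + 0.60 × 0.15 × 0.85 = 0.0955;
- V2-adjusted SE = √(2 × 0.0955 / 50) = 0.062.

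The size of this gain follows from the assumed 95% and 15%. It shrinks if V2 status predicts V4 less well.

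**Other scales.** For assumed two-category rates, going from 50 to 45 scored children per arm lowers power from 0.77 to 0.72 (20% v 45%), from 0.87 to 0.83 (30% v 60%), or from 0.53 to 0.49 (30% v 50%). As an extreme bound, take equal counts among the 45 observed per arm, with the 5 missing in each arm given opposite outcomes. The difference then moves by 5/50 = 10 points, with p about 0.29 to 0.32.

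**The case against.** The strongest reply is that the imputation paragraph may already cover this score. It applies to missing data of any cause, it provides logistic models for categorical variables, and it makes complete-case analysis a sensitivity analysis only. Its position under the Primary outcome heading does not settle its scope: the cLDA model is also specified only there and is then used for secondary outcomes. A reader might infer that the endpoint is certain to be analysed on complete cases alone. The documents do not support that; it is one of two readings. If the paragraph does not extend, missing-data handling for one secondary endpoint is a detail that an article may leave to the full protocol or SAP. What remains is that the article itself fixes a test that cannot supply what its pooling rule requires, so the passages do not connect even on the favourable reading.

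A reader might also infer that about 10% of children leave early and so lack a score. That is not supported either. The 10% is an allowance for non-analyzable data, and stopping the sleeve is not the same as missing V4.

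It is fair, too, that baseline is partly built into codes 1 to 3, which are relative to the first examination. That does not make the comparison of arms adjusted for V2 status: under the assumptions above, whether a child can plausibly reach code 0 still depends heavily on it.

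Finally, the bias figures rest on assumed rates and a strong imbalance in loss, and the Discussion expects good tolerance. This limits the size of the point and is accepted.

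**Conclusion.** The point holds in a limited form. The article assigns this endpoint to all randomized children and names a test that can use only those with a V4 score. That test ignores V2 status as a covariate and provides no estimate for Rubin's rules. Whether imputation is meant to reach the score is unclear.

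The likely effect is modest. There is no bias unless missing V4 scores both differ between arms and relate to baseline severity. Under the assumptions above, a fourfold difference in loss (16% v 4%) gives about 5 points and roughly 2 percentage points of extra type I error. The AHA conclusion is untouched. The firmer argument for change is that V2 adjustment removes that bias where it arises and improves precision even with complete data, by an amount that depends on how strongly V2 predicts V4.

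**What to change.** In the Secondary outcomes paragraph of Statistical analysis:

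1. Compare arms on the neuro-orthopedic score with a logistic or ordinal model containing arm and V2 status, or with a V2-stratified test where cells are sparse.
2. State that the multiple imputation covers this score, with V2 status in the imputation model.
3. Pool the arm effect by Rubin's rules.
4. Keep the chi-square or Fisher test on examined children as the complete-case sensitivity analysis.

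No new data are needed: the V2 examination is already scheduled, and Trial design describes coding and data handling as continuing to the end of 2022. The costs are some programming, reliance on the missing-at-random assumption that the plan already makes for its imputation, and possible sparse cells. The examination covers 11 mobilities in 100 children with a four-level score, so some categories may need to be combined or handled by the stratified test.

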#### Secondary outcomes

For all secondary outcomes, we will consider the variation between the inclusion (baseline value) and post-treatment value (6 months).

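### The 6-month neuro-orthopedic score merges full recovery with never abnormal, and the planned unordered test uses no baseline, so it loses power and gives no direction

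*Protocol article*

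**What the plan says.** The subsection on the neuro-orthopedic examination (Protocol article, Outcomes) sets the scoring. At baseline: "At the first examination, each mobility is scored on a binary scale (0 = normal range of motion, 2 = presence of anomaly". The 6-month results "are scored in comparison with the first examination", with the codes "0 = normal range of motion, 1 = lower anomaly, 2 = stable anomaly, 3 higher anomaly". The purpose is given just before: "The results obtained after this examination are scored so that changes can be analyzed". The opening sentence of Secondary outcomes, under Outcomes, sets the same aim for every secondary outcome: "we will consider the variation between the inclusion (baseline value) and post-treatment value (6 months".

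The Statistical analysis section names the 6-month 0 to 3 score as the outcome. Its Secondary outcomes subsection then fixes the test: "For the neuro-orthopedic examination, we will use a chi-square test or Fisher exact test if appropriate". QUEST, the PedsQL CP module and the SEP parameters get the baseline-constrained longitudinal model (cLDA) instead. The sensory findings are only described.

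**The concern.** Code 0 is the only 6-month code not defined by reference to the first examination. It therefore holds two groups with opposite meaning: mobilities that had nothing to improve, and mobilities with the best possible response. A chi-square or Fisher test on the four codes cannot tell them apart, because the baseline score does not enter. The test also treats the codes as labels without order, so a shift from stable to lower anomaly counts no differently from the reverse.

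Three things are at stake. A real benefit is harder to detect. A significant result does not say which way the arms differ, and the share of code 0 does not settle it. A chance difference between arms in baseline-normal mobilities feeds directly into the comparison. The Discussion in the abstract and the Conclusion both expect the secondary outcomes to inform the debate on mobility and tonus, and this outcome bears on both.

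**Working it through.** **Inputs.** The article gives no rates or sample size for this outcome. Its size for the primary outcome is 50 per arm, allowing 10% non-analyzable data: 50 × 0.9 = 45 analysed per arm, which matches the 45 stated. Alpha is 0.05, two-sided.

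**1. Pooling in code 0.** Take 50 children per arm and one mobility.
- Arm A: 30 always normal, 20 abnormal and stable. Codes 0/1/2/3 = 30/0/20/0.
- Arm B: 10 always normal, 20 normalised, 20 stable. Codes = (10 + 20)/0/20/0 = 30/0/20/0.

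The tables are identical, so chi-square p = 1. Among mobilities abnormal at baseline, 0/20 against 20/40 improved (Fisher p about 0.00004). The baseline imbalance is deliberately extreme, to show the mechanism.

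**2. Order ignored.** Take 15/20/10/5 against 15/10/20/5. The expected counts are 15/15/15/5 in each arm, so chi-square = 4 × 5²/15 = 6.67 on 3 df, p = 0.083. Swapping the labels for lower and stable anomaly leaves this unchanged, so the statistic carries no direction.

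**3. Power, by simulation.** All rates here are assumptions.
- Normal at baseline: code 0 in 95%, code 3 in 5%, both arms.
- Abnormal at baseline, codes 0/1/2/3: placebo 5/20/60/15%, active 15/35/42/8%.
- One mobility per child, 45 per arm, 5,000 to 10,000 trials per setting. Ranges show repeat simulations.

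| Normal at baseline | Planned chi-square | Wilcoxon, pooled score | Rank test, abnormal at baseline only | Rank test stratified by baseline |
|---|---|---|---|---|
| 0% | 55–56% | 71–72% | 71–72% | 71–72% |
| 20% | 34–35% | 38–40% | 60–61% | 59–61% |
| 40% | 22–24% | 18–19% | 49% | 44–45% |
| 60% | 15–16% | 9% | 34% | 28–30% |

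The pooled Wilcoxon falls below the chi-square at 40% and 60%. It ranks always-normal mobilities as better than improved ones, so the treatment signal is diluted.

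**4. Type I error.** With identical transition rates in both arms, the planned test rejects in 4.6 to 4.8% of trials.

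**5. Chance imbalance.** Again with no treatment effect, fix the baseline-normal counts at 18/45 and 27/45. The planned test then rejects in about 12 to 13% of trials, against about 2% when the counts are balanced. The rank test restricted to abnormal mobilities stays at about 5% in both cases. If half the mobilities are normal at baseline, a difference of 9 or more between arms arises in about 7% of randomised trials.

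**The case against.** Several stronger readings are tempting, and the document does not support them.

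- **That the outcome cannot measure improvement at all.** Codes 1 to 3 are scored against the first examination: code 1 is improvement, 2 is stability, 3 is worsening. Only code 0 is ambiguous, and the recorded baseline score can separate its two parts. The planned test does detect benefit in the simulations, though with low power.
- **That the test is invalid.** It is not. Under randomisation its overall type I error holds. The 12 to 13% is conditional on an uncommon imbalance, and sensitivity to such imbalance is common to unadjusted comparisons.
- **That range of motion and Modified Ashworth grades are thrown away.** No statement says so. The article records them ("Active range of motion is recorded for the same mobilities") and names the derived score as the outcome. Whether the raw measures are also summarised may stand in the full protocol or analysis plan. Modelling degrees with cLDA would replace the chosen outcome, which is a preference and not a correction.
- **That an ordinal test alone would do.** With many always-normal mobilities it can do worse than the chi-square, as the table shows.

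It is also fair to say that this is one of several secondary outcomes, discussed in exploratory language. What stands is narrower. The coding of 0 and the choice of test are both stated in the article, so this is not detail left to an unseen document. Together they fit poorly with the declared aim of analysing change.

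**Conclusion.** The point holds as a matter of efficiency and interpretation. Code 0 mixes no change with full recovery, and the planned comparison uses neither the baseline score nor the order of the codes. The result gives no direction and is exposed to chance imbalance in baseline-normal mobilities. With 45 per arm and 20 to 40% of mobilities normal at baseline, power is about 24 to 35%, against 49 to 60% for a rank test restricted to mobilities abnormal at baseline.

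Those figures rest on assumed transition rates, on one mobility per child, and on a new anomaly in a baseline-normal mobility being coded 3. Other rates would change the size of the loss. The pooling in code 0 and the disregard of order follow from the text alone. The change should be made, but nothing here touches the primary AHA analysis or the sample size.

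**What to change.** For the 0 to 3 score, restrict the analysis of change to mobilities abnormal at baseline, ordered normalised < lower < stable < higher anomaly, and compare the arms with an ordinal method such as proportional odds or Wilcoxon. Alternatively, keep all mobilities and stratify by baseline status (van Elteren). Report new anomalies in baseline-normal mobilities separately by arm. If mobilities are pooled across the arm, account for clustering within child.

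The baseline score is already recorded at the baseline visit, before the wearing period, so restricting on it does not select on response to treatment. The cost is some programming and a smaller set per mobility: with 45 per arm, about 45 × 0.8 = 36 at 20% normal and 45 × 0.6 = 27 at 40%. The power figures for the restricted test already include that loss. The article says that coding and data handling run to the end of 2022. The revised rule should be fixed and dated before allocation is revealed for analysis.

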## Discussion

The PROPENSIX study is the largest sample size RCT with double-blinding and placebo device, aiming to assess the efficacy of a PGT using compressive dynamic Lycra^®^ sleeve on bimanual performance in children with UCP aged 5 to 10.

To our knowledge, it is the first RCT aiming to involve 100 participants for the evaluation of PGT using Lycra^®^ sleeves in cerebral palsy. It is also the first large sample RCT to be conducted with participants and investigators being blinded regarding the intervention, thanks to a placebo device. A recent systematic review conducted by Almeida et al. [53] analyzed 13 studies covering 4 different types of Lycra^®^ garments; 6 studies were RCT with small sample size. The low statistical power of previous studies is limiting conclusions for clinical practice*.* Martins et al. [54] included 4 RCT in a meta-analysis, totalizing 110 subjects. It demonstrates a significant but small effect size on Growth Motor Function Measure (GMFM) at post-treatment, with moderate heterogeneity between trials. Moreover, the PROPENSIX protocol follows recommendations from Martins et al. [54] to use valid and reliable measures that assess all domains of ICF.

Another strength of the present study relates to the splint compliance and tolerance. We believe that the sleeve type of Lycra^®^ garment would bring a good acceptability and tolerance because it does not cover a large part of the body and lets the fingers free. Adverse effects are expected to be minor. Parent’s complaints concern the discomfort associated with more covering devices. In this protocol, we propose to continue wearing for at least 3 h a day, for a total of 6 months. The usual rehabilitation program of the child does not undergo major modifications. The child does his/her usual activities, rhythmed by the usual environment, in a context of confidence.

We wanted the major outcome to represent what we really want to enhance when we manage the rehabilitation of children with UCP. Bimanual performance, which designates what the child really does in an ecological context, is the principal measure outcome, assessed by the AHA.

The results of the SEP as a secondary outcome should emphasize the link between somatosensory dysfunction and motor ability. It could bring interesting arguments to discuss whether enhancement of motor function is subtended by enhancement of somatosensory function.

The age of the study population can be discussed. The 5–10-year-old frame allows a better involvement of the child in the rehabilitation program. However, fine prehension acquisition occurs earlier and it could be interesting to conduct similar studies in younger children. Regarding other potential limitations of the present protocol, we can cite the absence of long-term evaluation and the lack of a goal attainment specific scale, such as Goal Attainment Scaling (GAS) or Canadian Occupational Performance Measure (COPM).

